#### Return to activity

The *MARX Activity Rating Scale* (MARS) is a four-item activity rating scale. The patient is asked to rate how often they were able to perform each activity (e.g. running, cutting, decelerating, and pivoting) in their most healthy and active state. The patient is provided with five categories of frequency of each functional activity, ranging from less than one time in a month to four or more times in a week. One point is allocated for each category of frequency and a maximum score of 16 points can be awarded. The MARS has demonstrated excellent test-retest reliability and construct validity in patients with disorders of the knee [48].

We will look at return to sport by asking patients to report their primary sport and level of participation prior to injury. Following surgery, we will ask patients to record the date they returned to their primary sport and level and provide reasons they chose not to return if so indicated.

#### Adverse events and cost outcomes

We will record *adverse events* including wound complications, infections, painful hardware, re-operation (e.g. meniscal injuries, etc), and radiographic evidence of osteoarthritis (radiographs are part of routine care).

A research assistant at each site will contact patients who have experienced an adverse event to capture cost data associated with the event. The cost form consists of 12 domains (emergency room visits and hospitalizations, family doctor visits, specialist visits and outpatient clinics, health care professional visits, tests, procedures and surgeries, prescription medications, supplies and equipment, over-the-counter medications, employment statues and time-off work from paid employment, assistance from others, assistance living and transportation and miscellaneous costs) that patients self-report.

### Participant timeline

After the patient has been screened and signed the informed consent document, we will schedule a pre-operative baseline appointment. At baseline, we will have patients undergo a clinical assessment, range of motion, complete the seven patient-reported questionnaires along with demographics and a pre-op return to sport questionnaire, and perform the strength testing. Post-operatively, we will see participants at 3 months, 6 months, 12 months and 24 months for further follow-up (Table 2).

**Table 2 Tab2:** Participant Timeline

Assessments	Appointment					
	Baseline	Surgery	3 Months	6 Months	12 Months	24 Months
Demographics	X					
Surgery Forms		X				
ACLQOL	X		X	X	X	X
IKDC	X		X	X	X	X
KOOS	X		X	X	X	X
Euro-QOL	X		X	X	X	X
MARS	X		X	X	X	X
LEFS	X		X	X	X	X
P4	X		X	X	X	X
Return to Sport	X				X	X
ROM	X		X	X	X	X
Clinical Assessment	X		X	X	X	X
Radiographs	X				X	X
Adverse Event Form		X	X	X	X	X
Strength Testing	X			X	X	X
Hop Testing				X	X	X
Drop Vertical Jump Testing				X	X	
Root Tear MRI					X	X
Two Year MRI						X

### Recruitment

Patients presenting to the participating centres will first be diagnosed by an orthopaedic surgeon. After diagnosis, the surgeon will introduce and briefly outline the research study to the patient. The surgeon will then ask the patient if a member of the research team (graduate student or research assistant) can contact them with further information about the study. Upon receiving patient approval, a member of the research team will contact the patient with more information. The patient will be given the necessary time to consider participation in the study and will accept or decline once they have come to a decision.

Patients under the age of 18 will be provided with information about the study and will be asked to provide their consent along with legal guardian consent. Parents or guardians that are present at the appointment will be included in the informed consent process. If parents or guardians are not present the patient will be given the opportunity to discuss their participation with their parent or guardian before making a decision regarding trial participation.

### Randomization

#### Concealment mechanism/implementation

Potential participants will be screened by an independent clinician. Upon determining willingness to participate, confirming eligibility and meniscal status intra-operatively, a research assistant will enter the patient’s date of birth, sex and meniscus status before randomizing the patient via telephone or web-based randomization system to ACLR alone or ACLR with LET.

### Allocation (sequence generation)

All patients will be randomized by surgeon using a standard randomization design whereby each surgeon performs either ACLR alone or ACLR with LET in a 1:1 ratio. Randomization is stratified by surgeon, sex and meniscal tear status (presence or absence of meniscal repair requiring a change in postoperative rehabilitation) in permuted block sizes of two and four to ensure that the difference in outcome attributable to surgeon is equally dispersed between groups. Surgeons will be unaware of block order.

### Blinding

Surgeons, data collectors, and the data analyst will be blind to group allocation. The addition of a LET procedure results in a unique incision on the lateral side of the knee between the lateral epicondyle and Gerdy’s tubercle. The unblinded member of the research team will place an opaque adhesive across the lateral side of the knee covering the area where a LET incision could be seen for clinical assessment and range of motion. Clinical assessment will be completed by an independent assessor (an experienced surgeon that did not perform the surgical procedure on the patient). Participants will be asked to wear a tubigrip sleeve over the operative knee during all functional testing to conceal the incisions.

### Sample size

We estimate that within this group of high-risk patients that the absolute risk (AR) of graft failure (as defined above) in the ACLR group will range from 25 to 35%. We would consider a relative reduction in re-rupture rate of at least 40% to merit a change in practice (i.e. of sufficient magnitude to warrant the additional costs related to the procedure). Thus, with 255 patients per group and a type 1 error rate of 5% we would have approximately 80% power to detect a relative risk reduction (RRR) in rate of re-rupture in the LET of 40% or greater. Because we expect a combined withdrawal and lost-to-follow-up rate of about 15%, we will recruit a total of 600 patients (300 per group).

### Plan for statistical analysis

We will determine the absolute risk of graft failure in each group, calculate a relative risk (RR) and risk difference (RD) of graft failure with 95% confidence intervals around the estimate and use a Mantel Haentzel Test (random effect of surgeon) to determine the significance of the association between the addition of LET and graft failure rates. We will calculate the number needed to treat (NNT) to describe the number of patients who need to receive LET to prevent one graft failure over the first two postoperative years. We will calculate the mean and standard error (ACL-QOL, KOOS, EuroQoL) for each group at each time point and calculate the mean between-group difference with 95% confidence interval at 1 and 2 years postoperative. We will perform mixed model analyses, where time is a categorical fixed effect; treatment group, and sex are fixed effects, and patient and surgeon are random effects, to determine whether the difference between groups is of sufficient magnitude to make a definitive conclusion about the effectiveness of ACLR with LET compared to ACLR alone. Then, we will plot each health status score by time and by group to illustrate the change over time. We will conduct a similar analysis for all continuous outcome variables. Finally, for ease of interpretability, we will calculate the number of patients in each group who achieve a change at least as large as the MCID for an individual patient. We will present the NNT to describe the number of patients who need to undergo LET for one person to achieve an important change in HRQOL.

For qMRI analysis, T1rho and T2 relaxation maps are generated using software developed in-house by fitting image intensities of the T1rho and T2 weighted images pixel-by-pixel to the eq. S(TE) ∝ exp.(−TE/T2) using a Levenberg-Marquardt mono-exponential fitting algorithm. Load-bearing central, anterior, and posterior regions of medial and lateral articular cartilage of the femur and tibia are manually segmented and analyzed using 3D Slicer software. The reader is blind to scan order. We will use an independent t-test to evaluate whether the T1rho and T2 relaxation times between groups for all nine cartilage segments are statistically significant. We will present means, standard deviations and 95% confidence intervals for interpretation.

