## Background

The aim of anterior cruciate ligament reconstruction (ACLR) is to regain functional stability of the knee following anterior cruciate ligament (ACL) injury, allowing patients to return to their pre-injury level of activity. The reconstruction procedure has evolved significantly since the first ACLR was performed in the early 1900s [1] and while the techniques have changed, the goal of the surgery remains the same. A number of published meta-analyses have compared stability rates and functional outcomes of patellar tendon graft versus hamstring tendon graft and autograft versus allograft for ACL reconstruction [2–6]. The results have demonstrated that ACL reconstruction fails to restore normal knee stability [3, 5] regardless of graft choice, as rotational laxity [2, 4, 6] and anterior translation [2, 6] persist following surgery. Mohtadi et al. [7] conducted a level 1 randomized controlled trial comparing patella tendon (PT) grafts to single bundle hamstring (HT) and double bundle hamstring (DB) grafts. A significant number of patients in all three groups had rotational laxity characterized by a pivot shift greater or equal to 2 (HT – 19%; PT – 16%; DB – 21%). Abnormal tibial rotation has also been demonstrated in biomechanical assessment of traditional ACL reconstructions compared to the contralateral knee in functional tasks such as descending stairs [8], pivoting [8], and running [9]. Georgoulis et al. [10] later confirmed that a traditionally placed hamstring graft would not restore the normal knee joint kinematics. A positive pivot shift and ongoing rotational laxity has been shown to correlate with clinical outcome [11], which may be associated with graft failure and subsequent revision surgery. Studies investigating the epidemiology and risk factors for graft failure following an ACLR have found that younger patients (< 20 years old) [12–16], patients with physiologic knee hyperextension [17], and patients returning to pivoting sports [16] are at greater risk of re-injury.

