## Discussion

ACL injury is one of the most common orthopedic knee injuries and, despite advances in surgical technique and rehabilitation protocols, up to 30% of patients will re-tear their graft or suffer a contra-lateral ACL injury with younger age groups particularly at risk [16, 49]. Persistent instability leads to worse patient outcomes following ACLR and biomechanical cadaveric studies have shown that an ACLR alone may be insufficient to restore normal rotation. A 2015 meta-analysis of 29 studies (8 randomized, 21 non-randomized) comparing ACLR alone with ACLR and LET found the addition of a LET reduces rotational laxity by a statistically significant amount however, studies comparing the two procedures demonstrated limitations including small sample size and potential risk of bias [31].

The protocol for the *Stability Study* is the first adequately powered RCT to study the effects of whether augmenting ACLR with a LET reduces failure in young, high-risk patients. Two further potential strengths of this study are the addition of functional and biomechanical testing and quantitative MRI to the protocol. Functional and biomechanical testing are measures of neuromuscular training and patterning that require muscle strength, proprioception and balance to complete [50], all of which are important components in rehabilitation and injury prevention [51, 52]. Despite high re-injury rates and issues returning to pre-injury levels of sport following ACLR, few high-quality studies include comparison of functional and biomechanical outcomes between groups [53].

Concerns that the addition of an LET to the lateral side of the joint may increase the risk of post-traumatic OA will be addressed by the addition of qMRI to the trial. A recent systematic review found that radiographic evidence of OA was not significantly increased in patients where ACLR was augmented with LET compared to ACL alone [54]. Patients were assessed for radiographic evidence of OA however follow-up length and results were variable between studies. Using qMRI to evaluate cartilage degeneration allows us to compare articular cartilage health between groups through T1Rho and T2 relaxation times; increased relaxation times have been shown to be predictive of the development of OA [46].

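### The primary comparison accounts for surgeon but for no patient-level baseline risk factor, so a modest gain in precision is left unused

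*Protocol article*

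**What the plan says.** **Primary analysis.** The section Plan for statistical analysis states: "We will determine the absolute risk of graft failure in each group, calculate a relative risk (RR) and risk difference (RD) of graft failure". It adds 95% intervals, a number needed to treat over two years, and a Mantel-Haenszel test with a random effect of surgeon. No patient-level baseline variable is named for this comparison. In the same section, the mixed models for the continuous outcomes do carry sex as a fixed effect.

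**Randomisation.** Under Allocation (sequence generation) the strata are surgeon, sex and meniscal status. Under Concealment mechanism/implementation the research assistant enters "date of birth, sex and meniscus status before randomizing the patient", so age is known to the system but is not a stratum.

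**Risk factors in the article.** Background reports a greater risk of re-injury in "younger patients (< 20 years old"), in patients with knee hyperextension and in those going back to pivoting sport. It later hypothesises that a positive pivot shift predisposes to graft failure. Discussion speaks of re-tear or contralateral injury "with younger age groups particularly at risk". Eligibility criteria admits ages 15 to 25 and requires at least two of three features: competitive pivoting sport, pivot shift of grade 2 or more, and a Beighton score of 4 or more.

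**Planning figures.** Sample size assumes that "the absolute risk (AR) of graft failure (as defined above) in the ACLR group will range from 25 to 35" per cent, and continues: "We would consider a relative reduction in re-rupture rate of at least 40% to merit a change in practice". It then states that "with 255 patients per group and a type 1 error rate of 5" per cent "we would have approximately 80% power to detect a relative risk reduction (RRR") of that size.

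**The concern.** The trial defines its population by risk features and cites age as a risk factor, but the comparison that decides the trial uses none of them. They are not balanced by design either. With a binary outcome and power close to 80% at the low end of the planned control risk, adjusting for baseline variables that predict failure would usually give a somewhat tighter risk difference from the same patients.

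Timing also matters. If a visible imbalance in age or pivot shift appears at the end, an adjustment chosen after seeing the data is open to challenge. One fixed beforehand is not.

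**Working it through.** **1. Reproduce the planned sample size.** Inputs from Sample size: control risk 25% (low end of the range), 40% relative reduction giving 15%, type 1 error 5%, power 80%. Sidedness is not stated; two-sided is assumed.

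n per group = [1.960 × sqrt(2 × 0.20 × 0.80) + 0.842 × sqrt(0.25 × 0.75 + 0.15 × 0.85)]² / 0.10² = (1.109 + 0.472)² / 0.01 = 250, against 255 in the article.

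Power at 255 per group: z = (0.10 × sqrt(255) − 1.109) / 0.561 = 0.870, so power is 80.8%. At 35% v 21% the same formula gives 94.3%. Allowing for 15% loss, 255 / 0.85 = 300 per group. The plan's figures reproduce, and none of them relies on covariate adjustment.

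**2. Precision of the unadjusted risk difference.** SE = sqrt[(0.25 × 0.75 + 0.15 × 0.85) / 255] = 3.5 percentage points. The 95% margin is 1.96 × 3.5 = about ±6.9 points, against a target difference of 10 points.

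**3. Gain from adjustment.** If the covariates explain a share R² of outcome variance, the variance of the adjusted risk difference is about (1 − R²) times the unadjusted variance. The effective n is then 255 / (1 − R²) and the SE shrinks by the factor sqrt(1 − R²). R² is not in the article; 0.01 to 0.10 is assumed.

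| R² | Effective n per group | Power, 25% v 15% | Fall in SE |
|---|---|---|---|
| 0 | 255 | 80.8% | none |
| 0.01 | 258 | 81.2% | 0.5% |
| 0.02 | 260 | 81.6% | 1.0% |
| 0.05 | 268 | 82.7% | 2.5% |
| 0.10 | 283 | 84.7% | 5.1% |

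The gain is worth 3 to 28 extra evaluable patients per group.

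**4. Is that range of R² reasonable?** Four binary factors (age under 20, pivot shift, sport, laxity) were simulated under the two-of-three entry rule. Assumed prevalences before that rule were 60%, 70%, 85% and 40%; overall failure risk was 20%. With an odds ratio of 1.5, 2 or 3 for every factor, R² is about 0.012, 0.034 or 0.082, and power is 81.2%, 82.1% or 84.0%.

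**5. Size of chance imbalance.** One SD of the shift in the risk difference is sqrt(R² × 0.20 × 0.80 × 2 / 255). For the three R² values in step 4 this is about 0.4, 0.7 and 1.0 points. It is a component of the 3.5-point SE, not an addition to it.

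**6. Cost if the covariates are useless.** In simulation with uninformative covariates, the powers with and without adjustment differed by only 0.2 points (81.3% v 81.1%). Type I error was 5.7% with adjustment and 5.6% without.

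**7. Events available.** 255 × 0.25 + 255 × 0.15 = 64 + 38 = about 102 at the planning assumptions.

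**The case against.** The strongest reply is that nothing here is wrong. A relative risk, a risk difference and a Mantel-Haenszel test are valid for a randomised binary outcome, and a covariate list is often left to an analysis plan that is not shown. That stands as far as validity goes. But the article does state its primary method, and it names covariates where they were wanted, in the mixed models. So the point is an improvement to a stated method, not a complaint about a missing detail.

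A reader might infer more than the article supports:

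- **That chance imbalance biases the result.** It does not. It is random error, already covered by the 95% interval and the type 1 error rate.
- **That the trial is underpowered without adjustment.** The stated power is met at 25% and well exceeded at 35%.
- **That age is the strongest predictor of the primary outcome.** No section ranks the factors. The Discussion remark covers contralateral injury too, and the primary outcome also counts symptomatic instability with a positive pivot shift. Pivot shift as a predictor is a hypothesis, and the laxity factor cited in Background is hyperextension, not the Beighton score.
- **That every grade and score is on file.** Eligibility gives thresholds and Table 2 lists only a clinical assessment at baseline, so recording of the full values is inferred.

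Two further limits stand. Restricting entry to ages 15 to 25 with two of three risk features narrows the spread of these factors, so the gain may lie near the low end. The power calculation is also for a plain two-proportion comparison, so the gain over the planned surgeon-based test has not been shown directly. The article does not say whether the relative risk and risk difference are themselves pooled over surgeon.

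**Conclusion.** The point holds as a cheap improvement. As written, the primary comparison accounts for surgeon only, while age, pivot shift and pivoting sport are known before randomisation, are linked to failure by the article itself and are not strata. The expected benefit is about 0.4 to 4 power points at 25% v 15%. This rests on an assumed R² of 0.01 to 0.10, a two-sided 5% test and 255 evaluable patients per group. At the upper end of the control-risk range power is already 94.3%, so the benefit there is mainly a slightly narrower interval. The planned analysis would not give a wrong answer; it would give a slightly less precise one.

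**What to change.** In Plan for statistical analysis, pre-specify that the primary relative risk, risk difference, number needed to treat (from the risk difference) and p-value come from one model, for example logistic, containing:

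- treatment;
- the randomisation factors: surgeon (handled as now planned), sex and meniscal status;
- a short fixed list: age at surgery as a continuous variable and baseline pivot-shift grade, plus the sport and laxity entry criteria as recorded.

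Standardise the model to a marginal relative risk and risk difference with robust 95% intervals, so that the quantities reported are still those the plan names. Report the crude risks and the planned Mantel-Haenszel result alongside. State how a missing baseline value is handled.

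The cost is analysis wording and a slightly more complex model. The plan needs no extra patients or visits. First confirm that pivot-shift grade and the entry criteria are recorded for each patient. With about 102 expected events and surgeon already in the model, the covariate list should stay short.

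### The only test named for the primary outcome, a Mantel-Haenszel test with a random surgeon effect, is misspecified, and one of its readings loses planned power at 25% control risk

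*Protocol article*

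**What the plan says.** The section Plan for statistical analysis in the protocol article gives the primary analysis in one sentence. Besides reporting the group-specific risks, the authors will "calculate a relative risk (RR) and risk difference (RD) of graft failure with 95% confidence intervals around the estimate". The significance test is named in the last part of that sentence: they will "use a Mantel Haentzel Test (random effect of surgeon) to determine the significance of the association". An NNT follows. No other test is named for the primary outcome.

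The same section describes a mixed model for the continuous outcomes, in which "treatment group, and sex are fixed effects, and patient and surgeon are random effects".

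The section Allocation (sequence generation) says: "Randomization is stratified by surgeon, sex and meniscal tear status". Blocks are of two and four, and "each surgeon performs either ACLR alone or ACLR with LET in a 1:1 ratio". So one of the three stratification factors enters the primary test, sex enters only the mixed model, and meniscal status enters no analysis in the article.

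The Sample size section expects that the risk "in the ACLR group will range from 25 to 35"%, looks for a "relative reduction in re-rupture rate of at least 40% to merit a change in practice", and states that "with 255 patients per group and a type 1 error rate of 5% we would have approximately 80% power".

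**The concern.** A Mantel-Haenszel test compares observed with expected events inside each stratum, holding the stratum totals fixed. It has no variance component, so a random surgeon effect cannot be part of it. At least three analyses could be meant:

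- a fixed-stratum Mantel-Haenszel test by surgeon;
- random-effects pooling of one two-by-two table per surgeon, as in a meta-analysis;
- a binary-outcome mixed model with a surgeon effect.

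They do not perform alike when surgeons contribute few events. Pooling needs a continuity correction for empty cells, and surgeons without events drop out. It also gives least weight to the tables with fewest LET failures, which pulls the pooled RR towards 1. At stake is the one confirmatory result: its power, its estimate, and whether the method is fixed before the data are seen.

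**Working it through.** **1. The plan's own figure.** Inputs from Sample size: control risk p1 = 0.25, 40% reduction so p2 = 0.15, 5% type I error (taken as two-sided), 255 per group.

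n = [1.960·√(2·0.20·0.80) + 0.842·√(0.25·0.75 + 0.15·0.85)]² / 0.10² = (1.109 + 0.472)² / 0.01 = 250 per group.

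Power at 255: z = (0.10·√255 − 1.960·0.5657) / 0.5612 = (1.597 − 1.109) / 0.5612 = 0.87, which gives 80.8%.

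At 35% against 21% the same formula gives 94.3%. Allowing for 15% loss, 255 / 0.85 = 300 per group, or 600. The stated figures reproduce as a plain two-proportion comparison. At 25% there is almost no spare power.

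**2. Events per surgeon.** The number of surgeons is not stated. Nine (one per listed site) is taken as the low end and 40 as a high end. With 510 analysed:

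| Surgeons | Patients per arm per surgeon | Expected LET failures (15%) | Expected control failures (25%) |
|---|---|---|---|
| 9 | 510/18 = 28.3 | 4.3 | 7.1 |
| 20 | 510/40 = 12.8 | 1.9 | 3.2 |
| 40 | 510/80 = 6.4 | 1.0 | 1.6 |

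Empty cells will be common from about 20 surgeons upward.

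**3. Power by reading, 25% against 15%.** There were 3,000 simulated trials per scenario: 600 patients, blocks of two and four within surgeon × sex × meniscal status, and 15% random loss. Assumptions not in the article are surgeons of unequal volume and a 40% meniscal stratum. Stratum effects were either absent or set at a surgeon SD of 0.5 on the logit with log-odds of 0.5 each for sex and meniscal status. Ranges cover the two settings. Pooling is DerSimonian-Laird on the surgeon log RRs with a 0.5 correction.

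| Analysis | 9 surgeons | 20 surgeons | 30 surgeons |
|---|---|---|---|
| Unstratified chi-square | 81-82% | 81-83% | 81-82% |
| Fixed-stratum MH by surgeon | 82% | 81-83% | 80-82% |
| Fixed-stratum MH by all three factors | 82% | 80-82% | 78-79% |
| Random-effects pooling by surgeon | 69-71% | 64-67% | 59-61% |

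With no treatment effect, MH by surgeon rejects in about 4 to 5% of trials and pooling in about 2 to 3%.

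Runs with other assumptions agree:

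- With 15/25/40 surgeons and a surgeon SD of 0.4, pooling has 67/63/57% power and a mean RR of 0.64/0.66/0.68 against a true 0.60. MH by surgeon has 81-82% power and an RR of 0.60.
- Another run with 9/20/30 surgeons gave 72/66/60% for pooling, with an RR of 0.62-0.67. Regression adjustment for the stratification factors gave 81-84%.
- A random-intercept logistic model with 9/15/25/40 surgeons gave 82/83/85/83% (400 trials each).

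**4. Higher control risk.** With 9/15/25/40 surgeons, pooling has 79/77/75/70% power at 30% control risk and 87/85/84/81% at 35%. The last value is within simulation error of 80%.

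**5. Strata left out.** Moving from surgeon alone to all three factors in the MH test changes power from 80-83% to 78-82%. Full cross-classification is sparse: 20 surgeons × 2 × 2 = 80 strata, and 510/80 = 6.4 patients in each. Type I error with surgeon alone stays at about 4 to 5%, even when sex and meniscal status affect the outcome.

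**6. Test against interval.** If the RR and RD intervals were crude, they would disagree on significance with MH by surgeon in about 1 to 4% of trials at the design effect. The crude RR interval would disagree with the pooled test in about 11 to 22%.

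**The case against.** The strongest reply is that this is loose wording. Surgeon is a randomisation stratum, so stratifying the test by surgeon is the natural intention, and the section already uses a random surgeon effect properly for the continuous outcomes. Both of those analyses keep the planned power. The article never mentions pooling, meta-analysis or a continuity correction. A separate SAP may also settle which covariates enter.

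Much of this stands, and it limits three inferences that a reader might draw:

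- **That the trial as planned has less than 80% power.** The text does not support this. The loss belongs to one of several readings and to the lower part of the 25 to 35% planning range.
- **That leaving out sex and meniscal status loses power.** Step 5 shows it does not, and a fully cross-classified MH test is if anything slightly worse.
- **That the RR and RD intervals are unstratified, so the interval and the p-value come from different analyses.** The article does not say how the intervals are computed. Even if they were crude, conflict with MH by surgeon would be rare.

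The reply does not rescue the sentence. The article does name the primary test, and names one that does not exist in that form. Because the same section separates fixed from random effects correctly, random effect cannot safely be read as another word for stratified. A later SAP would have to depart from the published wording whichever reading it chose.

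**Conclusion.** The primary test is misspecified as written and needs to be replaced by one defined method. The consequence is conditional. Under random-effects pooling of surgeon tables, power at 25% control risk falls from about 80% to about 57-72%, the RR moves from 0.60 to about 0.62-0.68, and the test is conservative. Under a fixed-stratum MH test by surgeon or a model with a surgeon effect, the planned power is kept. The pooling figures rest on an assumed 9 to 40 surgeons of unequal volume, assumed stratum effects and the pooling variant described. The direction was the same at every surgeon number tried.

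Using only one of three stratification factors is a lesser point: a mismatch between analysis and design with little or no cost in power and no inflation of type I error.

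**What to change.** Delete the random effect from the Mantel-Haenszel test and name one primary analysis from which the test, RR, RD, their 95% confidence intervals and the NNT (from that RD) all come.

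- **Preferred:** a regression for RR and RD, such as modified Poisson or logistic with standardisation, with treatment, sex and meniscal status as fixed main effects and surgeon as a fixed or random effect. State which, and how surgeons with very few patients are handled.
- **Acceptable:** a fixed-stratum MH test by surgeon, with matching MH-weighted RR and RD and their intervals.

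Avoid a Mantel-Haenszel test over the full surgeon × sex × meniscal cross-classification, because its strata are sparse.

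The cost is a change of wording before the outcome data are examined. Sex and meniscal status are entered at randomisation and surgeon is a randomisation stratum, so there is no new data collection and no change in sample size.

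### The mixed model listed for the repeated secondary scores has no group-by-time or baseline term, so its group coefficient is a visit average and not the planned 1- or 2-year difference

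*Protocol article*

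**What the plan says.** All of the following is in the protocol article.

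- **Model.** Plan for statistical analysis lists the effects: "time is a categorical fixed effect; treatment group, and sex are fixed effects, and patient and surgeon are random effects". No interaction, baseline covariate or meniscal term is named.
- **Its task.** The same sentence gives the model the job of deciding whether the group difference is large enough to "make a definitive conclusion about the effectiveness of ACLR with LET compared to ACLR alone".
- **Target times.** A separate sentence, placed before the model, says that the trial will report group means at each time point and "calculate the mean between-group difference with 95% confidence interval at 1 and 2 years postoperative". It does not say whether these differences come from the model or are adjusted for anything.
- **Scope.** The model is introduced for ACL-QOL, KOOS and EuroQoL and then extended: "We will conduct a similar analysis for all continuous outcome variables". Quantitative MRI is handled separately: "We will use an independent t-test to evaluate whether the T1rho and T2 relaxation times between groups".
- **Data available.** Under Participant timeline, patients at baseline "complete the seven patient-reported questionnaires along with demographics and a pre-op return to sport questionnaire". Table 2 repeats all seven questionnaires at 3, 6, 12 and 24 months.
- **Stratification.** Allocation (sequence generation) names surgeon, sex and meniscal tear status. The model carries the first two only.

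**The concern.** A model with time and group as main effects assumes the same group difference at every visit. The plan itself gives reason to doubt this. Its rehabilitation schedule allows return to sport from 9 months, and the Background places the problem in young patients going back to pivoting sport. The 3- and 6-month visits precede that exposure; the 12- and 24-month visits follow it. The plan also intends to plot scores by time and group, yet the model cannot represent curves that diverge.

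At stake is what the model-based conclusion on quality of life and function means. A late benefit would be diluted in the coefficient. The plan would also hold two answers, a model coefficient and a set of 1- and 2-year differences, with the stated conclusion resting on the one less suited to those time points. Leaving out the baseline score and meniscal status mainly costs precision.

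**Working it through.** **The plan's own figure.** The article gives no power figure for any continuous outcome. Its only one is for the binary primary outcome. With 25% v 15% (a 40% relative reduction), 255 per group and two-sided 5%, pooled variance gives

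(0.10 − 1.96·√(2·0.20·0.80/255)) / √((0.1875 + 0.1275)/255) = (0.10 − 0.0694)/0.0351 = 0.87,

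so power is 80.8%. Also 255/0.85 = 300 per group. Both agree with the Sample size section, and nothing below touches them.

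**What the group coefficient estimates.** Let δ be the vector of true visit-specific differences and V the within-patient covariance. With complete data the expected coefficient is (1′V⁻¹δ)/(1′V⁻¹1). A random patient intercept gives V compound symmetry, so the weights are equal and the coefficient is the plain mean of δ. Correlations of 0.3, 0.5 and 0.7 give the same values.

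The patterns below are assumed, as fractions of the 12- and 24-month effect. The baseline difference is 0 by randomisation.

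| Pattern at 3, 6, 12, 24 months | Postoperative rows only | With baseline rows |
|---|---|---|
| 0, 0, 1, 1 | 2/4 = 0.50 | 2/5 = 0.40 |
| 0.25, 0.5, 1, 1 | 2.75/4 = 0.69 | 2.75/5 = 0.55 |
| 1, 1, 1, 1 | 4/4 = 1.00 | 4/5 = 0.80 |

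Simulation check: 20 data sets, 255 per group, first pattern, baseline rows included. The listed model gave 0.41 of the true effect. With group-by-time added, the 12- and 24-month contrasts were 1.02 and 1.01.

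**Illustration of power.** Assumed, since the documents give no values: a 5-point effect, between-patient SD 12, within-patient SD 14, 255 per group, two-sided 5%.

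Standard errors:

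- Listed model, five visits: √(2·(144 + 196/5)/255) = 1.20.
- Listed model, four postoperative visits: √(2·(144 + 196/4)/255) = 1.23.
- Single-visit contrast: √(2·(144 + 196)/255) = 1.63.
- Single-visit contrast adjusted for baseline, r = 144/340 = 0.42: 1.63·√(1 − 0.42²) = 1.48.

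Power = Φ(effect/SE − 1.96):

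| True effect | Listed model, baseline rows | Listed model, postoperative rows | 24-month contrast | 24-month contrast, baseline-adjusted |
|---|---|---|---|---|
| 5 points at 12 and 24 months only | 2.0/1.20: 39% | 2.5/1.23: 53% | 5/1.63: 86% | 5/1.48: 92% |
| 5 points at every postoperative visit | 4.0/1.20: 92% | 5.0/1.23: 98% | 86% | 92% |

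In SD units, with an effect of 0.25 SD at 12 and 24 months only and correlations from 0.3 to 0.7, the listed model over five visits has 40% to 25% power. An unadjusted single-visit comparison has 81%, and a baseline-adjusted one 84% to 98%.

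**The case against.** The case on the other side has real force.

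- **The 1- and 2-year differences are planned.** A reader might infer that the plan cannot deliver these effects. The documents do not support that: they are promised with 95% confidence intervals, and in a randomised trial they are unbiased apart from missing data. What stands is that they are not linked to the model on which the conclusion rests.
- **Averaging over baseline is an inference.** The questionnaires are collected at baseline and time is categorical, so it is plausible, but the text never says that baseline scores are response rows. Dropping them does not cure the problem, because 3 and 6 months stay in the average.
- **The dilution depends on the pattern.** An average postoperative difference is a legitimate quantity, and under a constant effect the listed model matches or beats the 24-month contrast, as the last table shows. An early harm that cancels a late benefit is possible, but the documents give no figure for one.
- **Not every continuous outcome fits.** Hop and drop vertical jump tests have no baseline, the jump test is done only at 6 and 12 months, and quantitative MRI uses a t-test.
- **Baseline is not wholly unused.** The analysis of patients reaching the minimal important change uses individual change.
- **Detail may be in an unseen analysis plan.** That would excuse silence. Here the article lists the effects, and an analysis plan that followed the list would carry the fault.

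**Conclusion.** The point holds for the repeatedly measured continuous secondary outcomes, above all the seven questionnaires taken at all five visits. As listed, the model yields one visit-averaged difference, while the plan names 1 and 2 years as the times of interest and draws its conclusion on effectiveness from the model. The coefficient is 0.50 of a benefit confined to 12 and 24 months, and 1.00 of one that is constant after surgery (0.40 and 0.80 if baseline rows are included). This rests on complete data, compound symmetry and assumed effect patterns. The power figures rest further on an assumed effect size and assumed SDs.

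A reader might take the wording about a definitive conclusion to mean that the trial's main result is at risk. It is not: graft failure has its own analysis, and the primary composite and sample size are unaffected. This is a secondary-analysis fault that is worth correcting before the data are analysed.

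**What to change.** - Fit the postoperative visits as outcomes, with group, visit, group-by-visit, baseline score where collected, sex and meniscal status as fixed effects, and patient and surgeon as random effects. Alternatively, keep baseline as a response and constrain the two groups' baseline means to be equal.
- Take the planned 12- and 24-month differences with 95% confidence intervals from this model, and rest the conclusion on those contrasts.
- For hop and drop vertical jump tests, use the same model without the baseline term and report contrasts at the visits measured. The quantitative MRI comparison is outside this point.

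**Cost.** Analysis wording and a few more parameters; no new data. If the effect is in fact constant over visits, a single-visit contrast has less power than the average: in the illustration 86%, or 92% with baseline adjustment, against 98% for the listed model on postoperative rows.
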